#### Fugl-Meyer Motor Assessment

The Fugl-Meyer Motor Assessment evaluates upper and lower limb motor functions systematically [44]. The maximum score is 100, the upper extremity score is 66, and the lower extremity score is 34 [45].

#### Modified Barthel Index

ADL will be evaluated by the MBI [46]. The Barthel Index was first introduced in 1965 and consists of 10 items: feeding, personal hygiene, dressing, bathing, toileting, bowel control, bladder control, chair-bed transfer, ambulation or wheelchair, and stair climbing [47]. The BI was modified in 1989 to improve content reliability and internal consistency, resulting in the MBI [48]. Each item’s score ranges from 0 to a maximum that varies from 5 to 15. The score indicates the ADL ability range from inability to independence. Higher scores suggest better functional and independent ADL abilities, thus a score of 100 means total independence.

#### 36-Item Short Form Health Survey

Health-related quality of life is measured using the Chinese version of the 36-item Short Form Health Survey [49]. This questionnaire consists of 36 items related to physical and mental health, which are grouped in eight dimensions: physical functioning; role-physical, or the limitation in daily role functioning due to physical problems; role-emotional, or the limitation in daily role functioning due to emotional problems; bodily pain; general health perception; vitality; social functioning; and mental health perception, relating to physical and mental health respectively [50].

#### Functional Magnetic Resonance Imaging

Resting-state functional magnetic resonance imaging (fMRI) will be used in this study to examine longitudinal changes for cognitive impairment patients after stroke, and to investigate the relationship between imaging changes and cognitive recovery [51]. Subjects will be scanned twice (before and after treatment), using a 3.0 T signal MRI scanner (GE Healthcare, Little Chalfont, UK) with a birdcage head coil [52].

#### Event-related potentials

Cognitive function will be measured by event-related potentials (ERPs). ERP P300 is related to cognitive function closely, which can reflect information processing speeds, attention, and the updating of working memory [53]. Reaction time and correctness rates (correctly pressing the button for target and non-target stimulus presentations) will be measured to quantify the cognitive function, using the software system of Neuroscan ERPs (SynAmps^2^ Model 8050, Compumedics USA, Ltd, Charlotte, USA)

### Safety assessments

Whenever an adverse event (AE) occurs during the treatment or follow-up period, the medical staff will manage it accordingly, while researchers will document any AE in detail. Every participant will have the right to report AEs at any given point in time during this trial, and will receive appropriate medical attention. Serious AEs will be immediately reported to the primary investigator and the Human Research Ethics Committee of FJTCM to determine whether the participant needs to be withdrawn from the study.

### Economic evaluation

Cost-effectiveness and incremental cost-effectiveness (the required cost of improvement in cognitive function) ratios, will be the primary economic outcomes in this trial [54]. The cost of interventions comprises direct costs and indirect costs. Any expenses involving rehabilitation treatments, rehabilitation assessment fees, auxiliary equipment, and other direct medical expenses associated with stroke or direct non-medical cost (including rehabilitation related transportation, special diets, nurse escort fee, and other costs related directly to the medical expenses) throughout the rehabilitation period are classified as direct costs. In addition, the number of workdays lost by participants during the treatment and follow-up period will be used to evaluate indirect costs. Incremental quality adjusted life years will be the total of difference in duration of rehabilitation effects as weighted by cognitive function between intervention group and control group during the treatment and follow-up period.

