Further evidence and recommendations for clinical practice supporting a therapeutic regimen of TCM rehabilitation are currently insufficient. Although many studies have addressed the potential use of acupuncture to improve cognitive function, few have explored the effects of a therapeutic regimen of TCM rehabilitation in patients with PSCI [26, 27]. Because of limitations in design or sample size, some of these studies provided equivocal results, thus enhancing the need to conduct high methodological quality trials with large samples and longer follow-up periods. The purpose of this randomized controlled trial is to test the cost-effectiveness of TCM rehabilitation therapy and confirm its effectiveness for PSCI treatment.

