### Outcome measures

In this study, all the primary and secondary outcomes measures will be tested at baseline (−2 to −1 week) and after the intervention period (12 weeks). After follow-up (36 weeks), the cognitive function, quality of life, and ADL outcomes (MMSE, MoCA, SF-36, and MBI) will also be evaluated. All outcome assessments will be independently performed by experienced and blinded assessors. A summary of all the measures in the trial is shown in Table 1.

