### Statistical methods

All data will be analyzed using SAS version 8.2 (SAS institute Inc., Cary, NC, USA) by an independent blinded statistician. A statistical significance level of 0.05 will be used. For statistical description, continuous variables will be presented for each group using the mean ± standard deviation for normal distribution, and median and interquartile range for non-normal distribution. Categorical variables will be presented by using proportions with their standard error. In order to compare the primary and secondary outcomes between groups, measured at baseline, post-intervention and post-follow-up, the t-test or Mann–Whitney U test will be used for continuous variables and the Pearson chi-squared or Fisher’s exact test will be used for categorical variables. Non-parametric tests, Pearson chi-squared test, or Fisher’s exact test will be used for expressing changes in effect sizes of primary and secondary outcomes between groups before and after treatment, and during the follow-up period (at 12 weeks and 24 weeks).

To adjust the confounding influence if necessary, a general linear model or linear regression will be applied for dependent continuous variables, and a logistic regression model for dependent categorical variables. The analysis of the primary outcome will be expressed by using full analysis set with the principle of intention-to treat and the per-protocol set. The analysis of the secondary outcomes will be performed using the per-protocol set. The analysis of AE will be undertaken by using a chi-square test or Fisher’s exact test. Lastly, the economic evaluation will be assessed using cost-effectiveness analysis. Missing data will be imputed by the last observation carried forward rules.

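### The quantity the protocol calls incremental QALYs is weighted by cognitive function, not by a health utility, so it is not a QALY; the primary cost-effectiveness ratio is unaffected

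*Protocol article*

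**What the plan says.** Cost-effectiveness is a stated aim. The Background section says: "The purpose of this randomized controlled trial is to test the cost-effectiveness of TCM rehabilitation therapy". The Economic evaluation section then names two things.

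- The primary economic outcomes: "Cost-effectiveness and incremental cost-effectiveness (the required cost of improvement in cognitive function) ratios, will be the primary economic outcomes in this trial".
- A QALY quantity: incremental QALYs are the summed "difference in duration of rehabilitation effects as weighted by cognitive function between intervention group and control group", over treatment and follow-up.

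The Statistical methods section adds only that "the economic evaluation will be assessed using cost-effectiveness analysis".

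Quality of life is handled elsewhere, as a secondary outcome: "Health-related quality of life is measured using the Chinese version of the 36-item Short Form Health Survey". Of the instrument the protocol says: "This questionnaire consists of 36 items related to physical and mental health, which are grouped in eight dimensions". The Outcome measures section and Table 1 schedule it at baseline, 12 weeks and 36 weeks. Nothing in the article connects the SF-36 to the economic evaluation.

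**The concern.** The weight is what makes a QALY a QALY. It must express how people value a state of health, on a scale where 0 is dead and 1 is full health, so that a year gained in one condition can be compared with a year gained in another. The protocol names the quantity and also names its weight, and the weight is of the wrong kind. A test of orientation, memory, attention and language does not say how a state of health is valued. It is also blind to things this trial itself measures separately: motor function with the Fugl-Meyer, and bodily pain, mental health and role limitation with the SF-36.

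What is at stake is a labelled result. A reader who sees incremental QALYs will take them as comparable with QALYs from other studies, and a cognition-weighted figure does not support that. It would also look like a second, broader economic finding while carrying mostly the same information as the cognitive outcome.

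**Working it through.** The article states no QALY, utility or cost-effectiveness figure, so there is nothing to reproduce. The main check is a comparison of sections; the arithmetic after it is only an illustration.

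**Step 1: compare the definition with what a QALY requires.**

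| Element | What a QALY needs | What the article gives |
|---|---|---|
| Weight | Preference-based utility | Cognitive function (Economic evaluation) |
| Anchors | 0 dead, 1 full health | None stated; the MMSE is a 30-point test (Primary outcomes) |
| Coverage | Overall health | Cognition only; motor function, pain and mental health sit in other instruments |
| Time points | Repeated over the horizon | Baseline, 12 and 36 weeks, for MMSE, MoCA, SF-36 and MBI (Outcome measures, Table 1) |

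The first three rows fail. The fourth shows that the schedule would support a proper calculation from the SF-36.

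**Step 2: how much does the quantity repeat the primary ratio?**

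Assumptions, because the article does not fix these: the weight is MMSE/30, the groups are equal at baseline, and the difference is linear between visits. Let d12 and d36 be the MMSE differences at weeks 12 and 36. The trapezoid area in years is

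[12 × d12/2 + 24 × (d12 + d36)/2] / (30 × 52) = (18 × d12 + 12 × d36) / 1560.

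If a difference d is reached at week 12 and held to week 36, this is 30d/1560 = d/52. Under these assumptions the so-called QALY gain is the MMSE difference divided by 52, and cost per such unit is 52 times the cost per MMSE point. No new information about health enters.

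The Sample size section gives a gain of 3.52 points compared with control. With that figure:

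- held to week 36: 3.52/52 = 0.068;
- lost entirely by week 36: 18 × 3.52/1560 = 0.041.

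The most that 36 weeks can hold is 36/52 = 0.692.

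**Step 3: what would a utility-based figure be?**

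The documents give no utility values. For an assumed utility difference u, reached at week 12 and held, the gain is 30u/52:

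| Assumed u | QALYs gained |
|---|---|
| 0 | 0 |
| 0.01 | 0.006 |
| 0.02 | 0.012 |
| 0.05 | 0.029 |
| 0.10 | 0.058 |

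Nothing in the documents links a 3.52-point MMSE gain to any row of this table. The figure depends on the weight chosen, and the size of the discrepancy cannot be derived from the protocol.

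**The case against.** The strongest reply is that the protocol does not promise a cost-per-QALY analysis. Its primary economic outcomes are ratios per improvement in cognitive function, and its statistical section speaks of cost-effectiveness, not cost-utility. It mentions no willingness-to-pay threshold and no comparison with other QALY studies. The QALY appears in one sentence. All of this is correct, and it limits the point to that one quantity.

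It also rules out several stronger readings that a reader might infer:

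- **That the whole economic evaluation is invalid.** It is not. Cost per unit of cognitive improvement is a legitimate ratio, and it can meet the stated cost-effectiveness aim.
- **That cognition is counted twice.** Double counting needs both quantities in one sum or ratio. Here they are two separate summaries, so the fair word is redundancy.
- **That the incremental cost-effectiveness ratio is undetermined.** The protocol's own ratio has measured cognitive improvement as its denominator. The uncertainty shown in the working applies only to a cost-per-QALY ratio, which the protocol does not state.
- **That the SF-36 as described already yields utilities.** Its eight dimension scores are not utilities. Item responses, an algorithm and a value set are needed, and the article names no algorithm or value set.

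A second reply is that the article condenses a fuller protocol, which may define the scale, its anchors or a conversion to utility. That would excuse silence, so the absence of such detail is not the complaint. But the article is not silent about the weight: it states it. A fuller document that used a utility would contradict this sentence. What remains of the reply is some uncertainty about what would actually be computed.

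**Conclusion.** The point holds, confined to the quantity labelled incremental QALYs. As defined, it is cognition-weighted time. It is not a QALY, cannot be compared with other cost-per-QALY results, and largely restates the primary economic outcome. The definition should be corrected before any result carries that label.

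The size of the error cannot be given, because the documents contain no utility values. The 0.041 to 0.068 in the working rests on an assumed MMSE/30 weight and assumed time courses, and the 0 to 0.058 on assumed utility differences. Together they show only that the result depends on the weight. The primary endpoint, the sample size, the effectiveness analysis and the primary economic ratios are untouched.

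**What to change.** Delete the cognition weighting from the QALY sentence, then take one of two routes.

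1. **Keep QALYs and define them.** Compute the area under the curve of utilities derived from SF-36 item responses at baseline, 12 and 36 weeks. Name the algorithm (for example SF-6D) and the value set, and adjust the between-group difference for baseline utility. Report cost per point of cognitive improvement separately, as already planned.
2. **Drop the term QALY** and report only cost per point of cognitive improvement.

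Route 1 needs no new visit or questionnaire. It does need item-level SF-36 responses to be kept and a suitable value set to be available. It also needs an explicit caution, because self-report is less dependable in cognitively impaired patients. Route 2 costs one edited sentence and gives up any cost-utility result.

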### Data collection and management

Firstly, screeners are responsible for the acquisition of demographic and baseline characteristic data when the participants are recruited. Outcome assessors play an important role in evaluating the primary and secondary outcomes at baseline, 12 weeks (end of intervention), and 36 weeks (after the 24-week follow-up period). In each center, after the source data has been added to the case report form, two research assistants who are not engaged in either treatment or evaluation will enter those source data into an electronic data capture database through the scientific research management platform of FJTCM. Only the project manager has the right to log into every center’s database. Moreover, a statistical manager will be in charge of initial data organizing, identifying, coding, and converting data to make sure the format is proper for data analysis. Meanwhile, double data entry will be used to promote data quality. All materials related to the participants’ privacy will be kept confidential by the way of coding. Besides, all study documents will be retained securely for five years after completion of the study, and the result of our study will be published in open access journals.

Moreover, this trial has been monitored for safety control by an independent Data and Safety Monitoring Board (DSMB), consisting of two senior therapists and one rehabilitation physician who are experienced in post-stroke cognitive impairment and have no direct involvement in the study. The DSMB is an independent board and is responsible for source data validation, and AE management and reporting. For safety concerns, the DSMB may have the right to recommend termination or modification of the research, according to their clinical judgment.

### Statistical methods

All data will be analyzed using SAS version 8.2 (SAS institute Inc., Cary, NC, USA) by an independent blinded statistician. A statistical significance level of 0.05 will be used. For statistical description, continuous variables will be presented for each group using the mean ± standard deviation for normal distribution, and median and interquartile range for non-normal distribution. Categorical variables will be presented by using proportions with their standard error. In order to compare the primary and secondary outcomes between groups, measured at baseline, post-intervention and post-follow-up, the t-test or Mann–Whitney U test will be used for continuous variables and the Pearson chi-squared or Fisher’s exact test will be used for categorical variables. Non-parametric tests, Pearson chi-squared test, or Fisher’s exact test will be used for expressing changes in effect sizes of primary and secondary outcomes between groups before and after treatment, and during the follow-up period (at 12 weeks and 24 weeks).

To adjust the confounding influence if necessary, a general linear model or linear regression will be applied for dependent continuous variables, and a logistic regression model for dependent categorical variables. The analysis of the primary outcome will be expressed by using full analysis set with the principle of intention-to treat and the per-protocol set. The analysis of the secondary outcomes will be performed using the per-protocol set. The analysis of AE will be undertaken by using a chi-square test or Fisher’s exact test. Lastly, the economic evaluation will be assessed using cost-effectiveness analysis. Missing data will be imputed by the last observation carried forward rules.

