## Abstract

**Background:**

Post-stroke cognitive impairment (PSCI) lessens quality of life, restricts the rehabilitation of stroke, and increases the social and economic burden stroke imposes on patients and their families. Therefore effective treatment is of paramount importance. However, the treatment of PSCI is very limited. The primary aim of this protocol is to propose a lower cost and more effective therapy, and to confirm the long-term effectiveness of a therapeutic regimen of Traditional Chinese Medicine (TCM) rehabilitation for PSCI.

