**Methods/Design:**

A prospective, multicenter, large sample, randomized controlled trial will be conducted. A total of 416 eligible patients will be recruited from seven inpatient and outpatient stroke rehabilitation units and randomly allocated into a therapeutic regimen of TCM rehabilitation group or cognitive training (CT) control group. The intervention period of both groups will last 12 weeks (30 minutes per day, five days per week). Primary and secondary outcomes will be measured at baseline, 12 weeks (at the end of the intervention), and 36 weeks (after the 24-week follow-up period).

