### Sample size

The sample size calculation is based on the improvement of MMSE scores, which is used as the primary effect indicators to estimate. According to the similar published articles [29], the mean difference in MMSE scores before and after treatment is three points, with a standard deviation of 1.5. According to our pilot study, a therapeutic regimen of TCM rehabilitation (CT + acupuncture) can probably improve the MMSE by 3.52 points on average compared to the control group. Improvement will be measured according to the same size of the estimation formula:1$$ \mathrm{n}=2\left[{\left({u}_{\alpha }+{u}_{\beta}\right)}^2{\sigma}^2\right]/{\delta}^2 $$

With a type I error of 5 % (α = 0.05) and 90 % power (β = 0.10), it is estimated that a sample size of 173 participants per group will be required. Considering a 20 % dropout rate during the study, a minimum of 416 total participants is needed to reach the target 208 participants per group.

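### The sole primary outcome, MMSE, is tested at an unadjusted 0.05 at both 12 and 36 weeks, and the protocol does not name the deciding visit or measure

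*Protocol article*

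**What the plan says.** - **Outcome and visits.** The Primary outcomes section lists MMSE alone. The abstract gives the schedule: "Primary and secondary outcomes will be measured at baseline, 12 weeks (at the end of the intervention), and 36 weeks (after the 24-week follow-up period". The Outcome measures section confirms that MMSE is among the measures repeated at 36 weeks: "the cognitive function, quality of life, and ADL outcomes (MMSE, MoCA, SF-36, and MBI) will also be evaluated". Table 1 marks MMSE after the intervention and again after follow-up, and ranks neither visit above the other.
- **Tests.** Statistical methods sets one level, "A statistical significance level of 0.05 will be used", and then prescribes a t-test or Mann–Whitney test for continuous outcomes: "In order to compare the primary and secondary outcomes between groups, measured at baseline, post-intervention and post-follow-up". A further sentence adds non-parametric or categorical tests for "changes in effect sizes of primary and secondary outcomes between groups before and after treatment, and during the follow-up period (at 12 weeks and 24"; both figures in that bracket are in weeks. The primary outcome is to be analysed in both the full analysis set and the per-protocol set, with adjusted models where thought necessary.
- **Sizing.** The Sample size section works from MMSE improvement, citing a study in which "the mean difference in MMSE scores before and after treatment is three points". It sizes a single comparison: "With a type I error of 5 % (α = 0.05) and 90 % power (β = 0.10"). No week is given.
- **Aim.** The abstract's primary aim has two parts. One is to propose a cheaper and more effective therapy; the other is "to confirm the long-term effectiveness of a therapeutic regimen". The end of the Background section states the purpose as cost-effectiveness and effectiveness, without mentioning the long term.

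**The concern.** The trial was sized for one MMSE comparison at 5%, but the analysis section sets out at least two tests of MMSE after randomisation, each at the full 0.05. It gives no order of testing, no split of the level, and no rule that both visits must succeed.

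Two things are at stake. First, if the visits disagree, the protocol does not determine whether the trial succeeded: the sizing basis favours the end of treatment, and part of the aim favours the end of follow-up. Second, if either visit is allowed to count, the false-positive rate of the primary claim is no longer the stated 5%.

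**Working it through.** **1. The plan's own figure.** The stated formula is n = 2(u_α + u_β)²σ²/δ², with σ = 1.5, two-sided α = 0.05 and power 0.90. A difference of δ = 3.52 − 3 = 0.52 gives

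n = 2 × (1.96 + 1.28)² × 2.25 / 0.52² = 174.7, so 175 per group.

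The protocol states 173, which is within two patients. A one-sided test would give 143. Taking δ as 3.52 gives 4, and taking it as 3 gives 5 or 6. The stated size therefore fits one two-sided comparison of improvement at 0.05, with nothing set aside for a second test. (That δ is 0.52 is inferred from the arithmetic; the section does not say so.)

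**2. Two visits, one measure.** Let Z₁ and Z₂ be the test statistics at 12 and 36 weeks under no effect, with correlation ρ. The chance that at least one is significant is

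1 − P(|Z₁| ≤ 1.96 and |Z₂| ≤ 1.96).

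The protocol gives no value for ρ, so a range is assumed:

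| ρ | at least one visit significant (two-sided) |
|---|---|
| 0 (upper reference) | 1 − 0.95² = 9.75% |
| 0.5 | 9.1% |
| 0.7 | 8.3% |
| 0.8 | 7.8% |
| 0.9 | 7.0% |

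Repeated MMSE scores in the same patients will be clearly correlated, so 7.0% to 9.1% is the relevant range. Comparing changes from baseline at the two visits instead of scores gives a similar 7.7% to 9.1% over the correlation patterns tried.

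**3. Four tests, under one reading.** Suppose the sentence on changes means change from baseline at both 12 and 36 weeks, tested in addition to the scores. A multivariate normal simulation (1,000,000 draws per scenario, assumed MMSE correlations between 0.3 and 0.9) then gives at least one significant result in 13.7% to 16.1% of trials. The figure for four independent tests would be 1 − 0.95⁴ = 18.5%. Counting only results that favour the intervention, the range is 6.9% to 8.2%, against a nominal 2.5%.

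**4. If both visits had to be significant.** The chance of both being significant cannot exceed the chance of either one alone, so the error would be at most 5%. The inflation in steps 2 and 3 therefore depends on the decision rule, which the protocol does not state.

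**5. Cost of the remedies.**
- One named test at 0.05, or a fixed order of two tests, keeps the error at 5% and the sample size as stated.
- Splitting the level, 0.025 for each visit, would need 207 per group before dropout. Kept at 173 per group, power per test would fall from 89.7% to 83.7%.

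**The case against.** The strongest reply is that this is a condensed journal article, and multiplicity and testing order are commonly left to an analysis plan that is not shown. In addition, MMSE is the only primary outcome and the sizing on improvement before and after treatment already indicates the key comparison. The second part stands as a pointer but does not settle the matter: the Sample size section names no week, and Statistical methods does not carry the choice forward. The first part does not remove the point, because it does not rest on missing detail. The article itself prescribes several tests of the primary outcome at the same level.

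Other objections do limit what can be said:
- **Error rate.** A reader might infer that any significant MMSE result may be claimed, so that the error already is well above 5%. The protocol states no such rule. It leaves the rule open, and requiring both visits would not inflate the error.
- **Four confirmatory tests.** A reader might take the 14% to 16% as the trial's error rate. The sentence on changes is unclear. The part about the follow-up period may mean change from the end of treatment, and its label of 24 weeks differs from the 36 weeks used elsewhere. It may even describe another way of expressing the same comparison. The figure is one scenario.
- **Aim against sizing.** A reader might infer that the primary aim is the 36-week effect, in direct conflict with the sizing. Long-term effectiveness is only one part of the aim, so the text points two ways without contradicting itself outright.
- **Week 12 as the required choice.** The trial is sized on unadjusted improvement with no stated week. Week 12 is inferred from the end of treatment, and the sponsor may choose otherwise.

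**Conclusion.** The point holds as an undefined primary decision, with a conditional effect on type I error. The protocol tests its sole primary outcome at two post-randomisation visits at an unadjusted 0.05, and nowhere names the visit or measure that decides. If either visit may carry the claim, the two-sided false-positive rate is about 7.0% to 9.1%. The correlations behind that range are assumed, but the rate exceeds 5% throughout it. This core result does not depend on how the sentence on changes is read. The count leaves out the duplicate analysis in two patient sets and the optional adjusted model, neither of which is ranked.

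**What to change.** Before unblinding, name one primary test: one visit, one measure and one analysis set. An example that matches the before-and-after-treatment basis of the sample size is MMSE at week 12, compared between groups with adjustment for baseline MMSE, in the full analysis set. Test MMSE at week 36 at 0.05 only if that result is significant. If the sponsor regards the long-term effect as primary, use the reverse order. Label the remaining score, change, rank and per-protocol versions as sensitivity analyses. Reword the sentence on changes so that its reference point and its 24-week label are clear.

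This changes wording only. It uses data already scheduled for collection and needs no more patients. The price is that the confirmatory claim at the second visit depends on success at the first.

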### Primary outcomes

#### Mini-Mental State Examination

The Mini-Mental State Examination (MMSE), was first introduced by Folstein *et al*. in 1975 [35], and we will use the revised Chinese MMSE version [36]. It is a brief 30-point questionnaire, divided into 10 items: time and place orientation, short-term memory, attention and calculation, recall, language skills, repetition, complex commands, reading, writing, and copying of pentagons. When the resulting MMSE is 24 points or less, this means that the patient may suffer from some degree of cognitive impairment. The total score of the individual items demonstrates the recent severity of cognitive impairment.

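### The tests listed for between-group change include no comparison of means and are not split by variable type, so they do not match the mean MMSE improvement on which the trial is sized

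*Protocol article*

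**What the plan says.** Sample size section: "The sample size calculation is based on the improvement of MMSE scores, which is used as the primary effect indicators to estimate". The formula given is the one for comparing two means, fed with a mean and a standard deviation: "the mean difference in MMSE scores before and after treatment is three points, with a standard deviation of 1.5". The combined regimen "can probably improve the MMSE by 3.52 points on average compared to the control group". At a type I error of 5% and 90% power, "it is estimated that a sample size of 173 participants per group will be required".

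Primary outcomes section, on the MMSE: "It is a brief 30-point questionnaire, divided into 10 items". The only MMSE threshold in the article, 24 or less, marks impairment at entry and is not a definition of improvement.

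Statistical methods section: two consecutive sentences deal with group comparisons.
- The first covers outcomes at baseline, after the intervention and after follow-up. It splits by variable type: t-test or Mann–Whitney for continuous variables, chi-squared or Fisher for categorical ones.
- The second covers change: "Non-parametric tests, Pearson chi-squared test, or Fisher’s exact test will be used for expressing changes in effect sizes of primary and secondary outcomes between groups". It has no t-test and no split by type.

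The next paragraph allows a general linear model or linear regression for continuous outcomes, but only where adjustment for confounding is judged necessary. Adverse events have their own chi-squared or Fisher sentence.

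**The concern.** Improvement in MMSE is the quantity the trial is powered on, and the sentence that governs change lists no method for comparing mean improvement. It offers chi-squared and Fisher's exact tests for outcomes that are all numeric as described: scale scores, reaction times, error counts, a memory quotient, correctness rates, and imaging or ERP measures. Those two tests can reach a numeric change only after it has been cut into categories such as improved or not improved, and the article defines no such category.

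Two things are at stake. The first is consistency, since the analysis of change should estimate what the sample size was built on. The second is power, since a dichotomised change discards information and could not deliver the stated 90% at the planned size.

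**Working it through.** **Inputs.** From the Sample size section: SD 1.5, mean change 3 points, a stated effect of 3.52 points, alpha 0.05, power 90%, 173 per group, and 208 per group after the dropout allowance. Assumptions of this check: two-sided testing, normally distributed change, control mean change 3, the same SD in both groups, and the cut-offs shown in the table, none of which is in the article.

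**Step 1: reproduce the plan's figure.** n = 2(1.960 + 1.282)² × 1.5² / δ².
- δ = 3.52 − 3 = 0.52: n = 174.9, so 175 per group, within 3% of the stated 173.
- δ = 3.52, as worded: 4 per group.
- δ = 3: 6 per group.
- δ = 0.52, one-sided: 143 per group.

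Only 0.52 points, two-sided, comes near 173, so the stated 90% is checked on that basis.

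**Step 2: comparison of means, 173 per group.** SE = 1.5 × √(2/173) = 0.1613. Power = Φ(0.52/0.1613 − 1.96) = Φ(1.264) = 89.7%.

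**Step 3: rank test on the numeric change.** With asymptotic relative efficiency 3/π = 0.955, the effective size is 173 × 0.955 = 165.2 per group. Power = Φ(0.52/0.1650 − 1.96) = Φ(1.191) = 88.3%, a loss of 1.4 percentage points.

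**Step 4: chi-squared on a dichotomised change.** For a cut c, p₁ = 1 − Φ((c − 3)/1.5) and p₂ = 1 − Φ((c − 3.52)/1.5). With p̄ the mean of the two, power = Φ{[(p₂ − p₁) − 1.96√(2p̄(1 − p̄)/n)] / √([p₁(1 − p₁) + p₂(1 − p₂)]/n)}.

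| Cut (points) | p₁ | p₂ | Power, 173 per group | Power, 208 per group | n per group for 90% |
|---|---|---|---|---|---|
| 1 | 0.909 | 0.954 | 37.5% | 43.7% | 672 |
| 2 | 0.748 | 0.845 | 61.1% | 69.1% | 361 |
| 3 | 0.500 | 0.636 | 72.3% | 79.9% | 279 |
| 3.26 (best) | 0.431 | 0.569 | 72.8% | 80.4% | 276 |
| 4 | 0.252 | 0.374 | 68.8% | 76.7% | 302 |
| 5 | 0.091 | 0.162 | 50.7% | 58.3% | 463 |

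**Step 5: whole-point scores.** In 4,000 simulated trials with change rounded to whole points and 173 per group, power was 88.2% for the t-test, 87.0% for the rank test and 67.4% for chi-squared at 3 points or more. The ordering is unchanged.

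**Step 6: the literal effect.** If the difference between groups really were 3.52 points (means 3 and 6.52), a dichotomised test at 173 per group would have at least 98% power at the cuts tried (1, 3 and 4.76 points). The loss in Step 4 therefore depends on the 0.52-point reading.

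**The case against.** A reader might infer that the plan will cut MMSE change into categories and so forfeit its 90% power. The article does not support that. Nowhere does it say that change will be dichotomised. The sentence before the quoted one assigns tests by variable type, and the paragraph after it does the same with linear and logistic regression. The quoted sentence can be read as shorthand for that menu: rank tests for numeric change, chi-squared or Fisher for anything categorical. On that reading power is essentially kept, and a rank test is a legitimate choice for a bounded 30-point score.

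A reader might also infer that the analysis would yield no mean gain in MMSE points. That does not hold for the plan as a whole, which allows a linear model and reports mean ± SD for normally distributed data. The planned cost-effectiveness ratios can use those means whichever significance test is chosen.

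A third inference would be a raised false-positive rate. If the analyst could choose freely among the rank test and chi-squared at cuts of 2, 3, 4 or 5 points, the simulated chance of at least one p < 0.05 with no true effect is about 17%. Those cuts are invented for illustration, and the article proposes none. A responder definition, if one is wanted, may also sit in an analysis plan that is not shown, so the lack of a cut-off is not itself a fault.

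What the objection leaves standing is the wording. With no primary or secondary outcome defined as categorical, and adverse events covered elsewhere, the shorthand reading gives the chi-squared and Fisher clause nothing to act on. The linear model is conditional, so it is not the stated comparison of change.

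**Conclusion.** The point holds as a mismatch between two sections. The trial is sized on a difference in mean MMSE improvement, while the sentence on change lists only non-parametric, chi-squared and Fisher's exact tests, without saying which applies to numeric outcomes. The consequence depends on how that sentence is used:
- Rank test on numeric change: about 88% power against 90%, so little is lost.
- Chi-squared or Fisher on a dichotomised change: about 73% at best with 173 per group, about 80% with 208, and less at other cuts.

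The second figure is conditional. It rests on a categorisation the article does not state, on assumed cuts, on normal change with SD 1.5, and on the 0.52-point difference. The point deserves correction because the remedy is cheap and removes the ambiguity; it does not show that the planned power has been lost.

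**What to change.** In the Statistical methods section, replace the sentence on change with one that does the following:
- It limits Pearson chi-squared and Fisher's exact tests to truly categorical data, such as adverse events.
- It states that MMSE change is compared between groups on its full scale, as a difference in means with a 95% confidence interval, in line with the Sample size section. The linear model that the section already allows would serve.
- It keeps a rank test, if wanted, as a sensitivity analysis.
- It labels any responder proportion as descriptive, with its cut-off fixed before unblinding.

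This needs no new data, visits or patients. The small downside is that a responder p-value is no longer available as a main result.
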